## Sensitivity analyses

The analyses will be repeated on the mITT sensitivity cohort and the extended sensitivity cohort. The analyses will be repeated on the ITT cohort as an exploratory analysis.

### Durability analysis

These final analyses will be the same as the primary analysis (including sensitivity analyses) with the outcome defined until 36 months instead of 18 months.

### Interim analyses {21b}

Interim analyses are not planned for the study.

## Methods for additional analyses (e.g., subgroup analyses) {20b}

### Subgroup analyses

Analyses will be conducted for the following prespecified subgroups based on baseline covariates: presence of co-infections (chlamydia, gonorrhea, herpes simplex, trichomoniasis, syphilis, bacterial vaginosis), self-reported condom use, number of self-reported sex partners in the last 3 months (0–1 vs. 2+), contraception method, and PrEP use.

## Methods in analysis to handle protocol non-adherence and any statistical methods to handle missing data {20c}

### Missing data

Some participants may have a single positive HPV DNA test without another test in the required timeframe to determine persistent HPV. The primary efficacy analysis above will be repeated twice: once assuming all missing tests would have been positive and a second assuming all missing tests would be negative.

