#### Assumptions

Based on prospective data on HPV epidemiology in Africa, we anticipate 70% of young, sexually active women in Kenya will be HPV 16/18/31/33/45/52/58 naïve (as documented by baseline serology and HPV DNA) and eligible to contribute to an incident persistent HPV 16/18 and HPV 16/18/31/33/45/52/58 outcome. We assume the incidence of persistent HPV 16/18 to be 5 per 100 person-years and the incidence of persistent HPV 16/18/31/33/45/52/58 to be at least 5 per 100 person-years. We expect the efficacy of the bivalent and nonavalent vaccines to be 75% to prevent incident persistent HPV 16/18 infection due to lower geometric mean titers in observational data following single-dose versus three-dose vaccination [10]. To estimate the sample size, we assumed fixed follow-up time, i.e., all persons are followed for the same length of time, and loss-to-follow-up of 10%. The sample size estimate is based on a fixed number of events and the Hazard Ratio models (SeqDesign in R). For the null hypothesis, the HR = 1.0 and for the alternative hypothesis the HR = 0.25.

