#### Total sample size

Accounting for women who are HPV 16/18 DNA-positive or seropositive at baseline, we estimate that 2250 young women age 15–20 years would need to be enrolled (750 participants per arm). We estimated, with a 3:1 screening to enrollment ratio, approximately 9000 young women will be screened to identify 2250 eligible participants.

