## Statistical methods

### Statistical methods for primary and secondary outcomes {20a}

#### General statistical considerations

Descriptive analyses summarizing baseline and follow-up data will be stratified by site and/or country and treatment arm separately. Line, scatter, and box plots will be used, as appropriate, for longitudinal data representations. If loss to follow-up is greater than 10%, baseline characteristics will be described by loss to follow-up status. Missing data will be imputed.

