### Outcome

Outcome is as follows: Persistent HPV, defined as vaccine type specific HPV detected at two consecutive time points no less than 4 months apart after month 3 and up to and including 18 months apart (same HPV type at each time point) in the first 18 months post-randomization.

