### Analysis approach

The primary analysis will be performed on the mITT Cohort. If the participant does not reach the outcome of persistent oncogenic HPV infection, as defined above, her infection time will be censored at the last negative test date at or before the month 18 visit (time from month 3 visit to last negative test). A Cox proportional hazards (PH) model stratified by site will be used to assess the efficacy of each vaccine arm compared to control. Vaccine efficacy will be expressed as a percent reduction in the incidence rate (i.e., 100 × [1 − (vaccine infection rate/corresponding control infection rate)]). The log rank test stratified by site will be used to calculate the *p* value. Further details for the analysis are available in the statistical analysis plan.

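### One of the two planned missing-test reruns keeps the primary analysis's events unchanged, and the pair together does not in general show how low vaccine efficacy could fall

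*Protocol article*

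**What the plan says.** Four places in the protocol article bear on this.

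- **Outcome** (under Primary efficacy analysis) requires "vaccine type specific HPV detected at two consecutive time points no less than 4 months apart after month 3", with the same type at both, within the first 18 months.
- **Analysis approach** covers a woman who does not reach that outcome: "her infection time will be censored at the last negative test date at or before the month 18 visit".
- **Missing data** (item 20c) names the group at issue: "Some participants may have a single positive HPV DNA test without another test in the required timeframe to determine persistent HPV". The primary analysis is then repeated twice, "once assuming all missing tests would have been positive and a second assuming all missing tests would be negative". Neither rerun distinguishes between arms.
- **General statistical considerations** adds "Missing data will be imputed", without naming a variable, a method or an analysis.

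**The concern.** A sensitivity analysis for missing outcomes should show how far the result could move if the missing values were unfavourable. Here one rerun gives the unconfirmed women the status they already have in the primary analysis. The other changes both arms in the same direction, so movement in the numerator and denominator of the rate ratio can cancel.

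A reader could then see three nearly equal efficacy figures and take them as evidence of robustness, although no unfavourable case was examined. With about six events expected in a vaccine arm, one or two reclassified women move VE by several points. Missed confirming swabs are plausible: the article plans for 10% loss to follow-up, and its Discussion says research visits were restricted in March and April 2020, when women recruited between December 2018 and November 2019 were in follow-up.

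**Working it through.** **Step 1. Reproduce the planned events and power.** Inputs are from the Sample size section: "2250 young women age 15–20 years would need to be enrolled (750 participants per arm"), "We assume the incidence of persistent HPV 16/18 to be 5 per 100 person-years", "for the alternative hypothesis the HR = 0.25", 30% excluded, 10% lost and 1 year of follow-up. Two-sided alpha of 0.05 is an assumption; the article states none for the primary test.

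- Women per arm: 750 × 0.70 × 0.90 = 472.5
- Control events: 472.5 × 0.05 = 23.6
- Vaccine events: 23.6 × 0.25 = 5.9
- Total D = 29.5
- Freedman power: Φ(√29.5 × (1 − 0.25)/(1 + 0.25) − 1.96) = Φ(1.30) = 90.3%, against 90% stated

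With 48% excluded, D = 21.9 and power is 80.2%, against 80% stated. The plan's figures reproduce, so these event counts are used below.

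**Step 2. Trace one woman through the rules.** She is negative at month 6, positive at month 12 and has no month 18 test.

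| Analysis | Status | Time used |
|---|---|---|
| Primary | non-event | censored at month 6 |
| All missing negative | non-event | censored at month 18 |
| All missing positive | event | first detection at month 12 |

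The second row differs from the first only in the censoring date. For a woman first positive at month 18, no later swab falls inside the 18-month window and the two rows are identical.

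**Step 3. Size of the censoring effect.** A simulation used visits at months 3, 6, 12 and 18, 500 women per arm and 30 runs per setting. Assumed incidence was 5 and 1.25 per 100 person-years for persistent infection, and 8 and 2 for transient infection lasting 6 months (control and vaccine). VE is the mean Cox estimate.

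| Visits missing | Primary | All negative | All positive | Vaccine positive, control negative |
|---|---|---|---|---|
| 10% | 72.4% | 72.4% | 72.1% | 66.4% |
| 20% | 72.0% | 71.8% | 74.7% | 62.4% |

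The all-negative rerun had the same events as the primary in every run. The largest change in VE in any run was 0.4 points (10% missing) and 0.7 points (20% missing). At 20% missing, the all-positive rerun raised mean VE.

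**Step 4. What the pair can show on the planned events.** Let m_c and m_v be the unconfirmed positives in control and vaccine, with person-time held equal.

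- Primary and all-negative: VE = 1 − 5.9/23.6 = 75.0%
- All-positive: VE = 1 − (5.9 + m_v)/(23.6 + m_c)
- Vaccine positive, control negative: VE = 1 − (5.9 + m_v)/23.6

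| m_c, m_v (assumed) | Primary | All negative | All positive | Vaccine positive, control negative |
|---|---|---|---|---|
| 8, 2 | 75.0% | 75.0% | 75.0% | 66.5% |
| 4, 4 | 75.0% | 75.0% | 64.1% | 58.1% |
| 8, 8 | 75.0% | 75.0% | 56.0% | 41.1% |
| 0, 3 | 75.0% | 75.0% | 62.3% | 62.3% |

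The last two formulas agree only when m_c = 0. When m_v/m_c equals the event ratio of 0.25, the all-positive rerun does not move at all.

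**Step 5. What a tipping point would look like.** Hold control at 23.6 events and add k conversions in the vaccine arm. Approximate the log-rank statistic by z = (23.6 − V)/√(23.6 + V), with V = 5.9 + k.

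- k = 2: z = 2.80
- k = 4: z = 2.37
- k = 6: z = 1.97
- k = 7: z = 1.77

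Significance at the assumed level is lost at about seven conversions. The log-rate form, ln(23.6/V)/√(1/23.6 + 1/V), gives 1.93 at k = 6, so about six.

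**The case against.** The strongest reply is that the two reruns are simple extremes that the plan never presents as a lower bound. The trial is blinded for participants, site personnel and the HPV laboratory, so nothing suggests that confirming swabs are missed differently by arm or that their unknown results follow an extreme arm-specific pattern. The all-positive rerun is informative in some cases: with 4 unconfirmed per arm it takes VE from 75.0% to 64.1%. The month 36 analysis may also confirm some of these women later. All of this stands. It makes the arm-specific case a stress test, not an expected result, but it does not make the all-negative rerun informative.

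Four stronger readings are tempting and not supported.

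- A reader might infer that the all-negative rerun is identical to the primary analysis. It is not exactly so, because an assumed negative test can become the last negative test and postpone censoring. If all missing tests also covered a gap between two positives, it could even remove an event; the section's own wording limits it to single positives.
- A reader might infer that the pair can never show the least favourable figure. It does when the control arm has no unconfirmed positives.
- A reader might infer that efficacy would be overturned. In the 8-and-2 and 4-and-4 cases, z stays above 1.96 even under the arm-specific rule (k = 2 and k = 4 in step 5).
- A reader might infer that the general imputation sentence contradicts both other rules. Assumed test results are themselves a simple imputation, so there is no conflict with the reruns. Against the primary censoring rule the sentence is loosely worded, and its scope may be settled in the analysis plan that is not shown.

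**Conclusion.** The concern holds in a limited form. The all-negative rerun has the primary analysis's events and changed VE by less than 1 point under the assumptions tried. The pair therefore rests on the all-positive rerun, which is a lower bound only when control has no unconfirmed positives. On the planned events the unseen gap is 8.5 points (75.0% against 66.5%) with 8 control and 2 vaccine unconfirmed, and 6.0 points (64.1% against 58.1%) with 4 per arm.

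The sizes depend on the assumed numbers of unconfirmed positives, on the assumed missed-visit and transient-infection rates in the simulation, and on equal person-time in the table of step 4. That the all-negative rerun leaves the events unchanged follows from the article's rules for single positives and needs none of these figures. The primary analysis, its test and the stated power are untouched.

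**What to change.** Keep the all-positive rerun and replace the all-negative one with either of these:

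- a tipping-point analysis: how many unconfirmed vaccine-arm positives must convert, with control unchanged, before significance is lost, set beside the number actually unconfirmed; or
- an arm-specific rerun: confirming swabs that were due and missed are set positive in the vaccine arm and negative in control.

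Label it as a stress test, since the trial is blinded. Restrict it to swabs that were due, so that first positives at month 18 are not treated as missed confirmations.

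The cost is one changed rerun and a printed sensitivity figure that will be less favourable. No data collection changes.

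As a minor addition, the general imputation sentence could say that it does not override censoring at the last negative test in the primary analysis.

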## Plans to give access to the full protocol, participant-level data, and statistical code {31c}

The full protocol will be made available. Data cannot be shared publicly because this study was conducted with approval from the Kenya Medical Research Institute (KEMRI) Scientific and Ethics Review Unit (SERU), which requires that data from studies (including de-identified data) are released only after SERU have provided written approval for additional analyses. A complete de-identified dataset sufficient to reproduce the study findings will be made available upon written request after approval from SERU. To request these data, please contact the KEN SHE Scientific Committee at [contact].

### Composition of the data monitoring committee, its role and reporting structure {21a}

#### Data Safety and Monitoring Board review for safety and study execution

The Data Safety and Monitoring Board (DSMB) is independent and consists of six members: global expert clinical trial statistician, clinical trialists, experts in adolescent health including HPV infection, experts in cervical cancer treatment and prevention, and policy experts. The DSMB meets every 6 months to review the available study data. The DSMB evaluates participant safety (SAEs and social harms), available endpoint data, and reviews the operational factors, specifically participant enrollment and follow-up, to assess safety, study execution, and provide feedback for investigators on areas for attention.

#### DSMB stopping rules

We will plan a formal primary analysis to evaluate study outcomes after 18 months of follow-up. We will follow the policy recommendations for single-dose vaccination, given the expected emerging evidence from this and other clinical trials. Both the magnitude and durability of the effect through 36 months of the single-dose HPV vaccine are critical outcomes of this study.

## Adverse event reporting and harms {22}

The three sites monitor adverse events (AEs) according to the local guidelines of the KEMRI’s Scientific and Ethics Regulatory Unit (SERU), which is the site local regulatory authority. Adverse events are reported in the study data on eCRFs. Additional information about these AEs, including copies of outpatient records, hospitalization summaries, pathology reports, operative reports, and laboratory reports, are included in the reports as applicable. The SERU reporting process includes reporting all study-defined SAEs to SERU via email ([contact]) within 48 h after the PI (or official designee) becomes aware of the event. The hard copies of the report are forwarded to the SERU Secretariat within three working days of the initial notification. Follow-up reports are submitted as soon as more information becomes available. The written safety report is addressed to the SERU Chairperson and submitted to the SERU Secretariat. The reporting includes the PI’s (or official designee’s) opinion on the relationship of the adverse event with participation in the study.

## Social harm reporting

Although study sites make every effort to protect participant privacy and confidentiality, it is possible that participants’ involvement in the study could become known to others and that social harms may result. The three sites assess for study-related social harm at each scheduled follow-up visit; reports can also be filed at interim visits if study-related social harms are discovered between visits. Information regarding social harms related to study participation is recorded into the study database. Participants who report social harms are referred to speak with a study counselor and, if appropriate, a study clinician and the site investigator/designee. The three sites refer participants to appropriate additional resources for safety as needed. If the site investigator/designee judges a social harm related to study participation to be serious and unexpected, the study safety monitor and SERU is notified within 10 days of site awareness.

## Frequency and plans for auditing trial conduct {23}

The trial is being monitored by an independent study monitor every six months, which includes 100% quality checks of the vaccine randomization.

## Plans for communicating important protocol amendments to relevant parties (e.g., trial participants, ethical committees) {25}

Prior to implementation of this protocol, and any subsequent full version amendments, the three sites had the protocol and the protocol consent forms approved by SERU and Poisons and Pharmacy Board (PPB). Prior notice was given and written consent was sought and obtained from all study participants. All study participation is strictly voluntary, and participants can refuse specific procedures, or further study participation at any time.

## Protocol amendments

If changes are needed to the protocol, the protocol implementation team (in accordance with the protocol design team) handles all changes centrally. Once the changes are finalized, the protocol is submitted and approved by the appropriate IRBs and regulatory agencies prior to implementation. Version control is maintained centrally and sites will be trained on any changes.

## Discussion

This randomized, double-blind, controlled trial will provide data on single-dose HPV vaccine efficacy among adolescent girls and young women age 15–20 years. While observational evidence supports the efficacy of single-dose HPV vaccination [8, 10, 12], this study aims to provide estimates of efficacy to guide public health policy. Further, observational evidence supports multi-age cohort vaccination, up to age 26 years in high-income countries, as a key driver to prevent moderate and severe precancerous lesions over the shortest time period [6]. This strategy of multi-age cohort vaccination has been limited in low-and-middle-income countries by the high cost of the HPV vaccines, the limited supply, and the recommendation for three doses among persons older than 15 years. The KEN SHE Study aims to close that gap in evidence.

The final results of the KEN SHE study are expected in early 2023 and the primary results in Q1 2022. Other trials evaluating single-dose protection are ongoing in Costa Rica (the ESCUDDO trial; NCT03180034), the Gambia (the HANDS trial; NCT03832049), and Tanzania (the DoRIS trial; NCT02834637), with results available at the end of 2021 or later [9, 19]. These trials are all complementary, examining single-dose HPV vaccination for girls, adolescents, and young women age 4–20 years and address different scientific and programmatic questions. In addition to comparing efficacy between study groups, antibody results from A Dose Reduction Immunobridging and Safety Study of Two HPV Vaccines in Tanzanian Girls (DoRIS) Study will be used to immunobridge to the antibody results to the KEN SHE Study (by demonstrating non-inferior antibody levels) enabling extension of the single-dose approach down to girls age 9–14 years [19].

The study conduct has encountered and addressed challenges raised by the COVID-19 pandemic. During the global coronavirus (COVID-19) pandemic, as of May 17, 2021, Kenya has reported 165,465 cases, 3003 COVID-19 deaths, and a current case fatality rate of 1.8% [26]. Approximately 7000 SARS-CoV-2 tests were conducted daily in February 2021. Participant research visit were restricted in March and April 2020, but reopened in May 2020. Additional restrictions were in place in April 2021 with a third COVID-19 wave but these were lifted in May 2021 with a decrease in cases. Emergency services were available to participants throughout. WhatsApp discussion groups were started to facilitate participant retention, and visit questionnaires were completed by phone, with specimen collection resuming once SERU guidelines for in-person visits were in place. Clinical trial sites instituted COVID-19 safety precautions, following SERU guidelines, including symptom screening for participants and staff by phone prior to arrival at the clinic, temperature checks at the clinic, use of personal protective equipment, and social distancing where possible. Travel and in-person learning have re-opened with safety precautions to prevent SARS-CoV-2 transmission.

The KEN SHE Study data will contribute to the Global Strategy towards Eliminating Cervical Cancer as a public health problem led by the World Health Organization (WHO) [27]. Cervical cancer is the 4th most common cancer among women globally, and, the 2nd most frequent in sub-Saharan Africa (SSA), mostly affecting women between ages 30–49 years, and the leading cause of new cancer deaths in SSA [28, 29]. Cervical cancer is an almost entirely preventable cancer with HPV vaccine and the most curable form of human cancer with early detection and treatment. In August 2020, the WHO adopted the Global Strategy to eliminate cervical cancer by scaling up prevention through HPV vaccination—with the global target to reach 90% coverage of HPV vaccination by 2030, 70% coverage of screening and treatment of pre-cancerous lesions, and 90% coverage of management of invasive cervical cancer [27]. However, the estimated global coverage among 9–14-year-old girls for HPV vaccination is 40% with only 8–9% of 10–20 year olds vaccinated [30]. Further, HPV vaccine supply is constrained [7] and SAGE has called for options to optimally allocate existing HPV vaccine supply. Effective single-dose HPV vaccination would facilitate rapid scale up of vaccination worldwide or, in the absence of public health benefit, redouble efforts to ensure adequate supply and implementation of a two- or three-dose vaccination strategy to meet the goal of cervical cancer elimination.

The trial has several strengths including the randomized controlled blinded design, testing two vaccine types, and testing vaccine efficacy over a short time frame to support policy decisions. Further, the secondary objectives will evaluate immunobridging to younger trial participants, assess central memory for vaccine durability, and estimate the population-level impact on cervical cancer incidence and cost-effectiveness, building on the primary study results. A potential limitation of the study is not recruiting participants prior to sexual debut which may limit the number of HPV naïve participants eligible for assessment of vaccine efficacy.

In summary, the KEN SHE Study will evaluate single-dose HPV vaccination and provide robust estimates of vaccine efficacy against persistent HPV infection among adolescent and young women in sub-Saharan Africa. These data combined with other ongoing trials will provide evidence for policy makers on strategies to increase HPV vaccine coverage as a key component of cervical cancer elimination interventions.

